**POSSIBLE RISKS AND HAZARDS**

1. **Radiation exposure due to dual energy X-ray absorptiometry** -The radiation exposure due to DEXA is 2 mrem. A typical radiation dosage from a chest X-ray is 20 mrem. These values can be used to compare the relative risk of a total body scan by DEXA. For subjects that move excessively during the scan, a complete or partial repeat of the scan procedure may be necessary and thus these subjects could receive a maximum of 4 mrem per procedure.

2. **Questionnaires and computerized performance tests** - There are no known risks associated with completing any of these questionnaires or tests. However, as some of the questions may be of a highly personal nature, subjects will be informed that they do not have to respond to all the questions if they choose not to do so. If this is the case, notations to that effect will be noted in the patient’s record.

3. **Taste tests** - There are no known risks to performing these tests.

4. **Vending machines to assess actual fat intake** - There are no known risks to performing this test.

5. **Oral glucose tolerance test** - This test carries the risk of having an indwelling catheter in place for 3 hours. This includes hematoma, ecchymoses and infection.

6. **Twenty-four hour energy expenditure measurement in the respiratory chamber** - There are no known risks associated with this measurement. At any time, the subject can have visual or auditory contact with the nurses. A nurse is also charged with checking the temperature in the room as well as the different parameters listed on our computer screen every 4 hours. In case of any discomfort (cold, claustrophobia), the volunteer can leave the chamber.

7. **Blood drawing for hormone assessment** - This test carries the risk of developing a hematoma at the site of venipuncture.

8. **Actiheart and Actical activity monitors** - The activity monitors will include i) Actiheart - combined HR monitor and uniaxial accelerometer (chest-worn); ii) Actical – omnidirectional accelerometer (wrist, ankle, and/or hip-worn). The combined heart rate and movement monitor (Actiheart) clips on two standard EKG electrodes attached to the chest. This device has no buttons or display and is much lighter (8 grams) than any other movement sensors or heart rate monitors currently used in epidemiological research. The dimensions of the Actical are 28 x 27 x 10 mm, and it weighs 17 grams.

9. **CorTemp™ core body temperature monitoring system** – The system is intended for the measurement of continuous core body temperature. Contraindications for use are as follows:
 a. Volunteers weighing less than 80 lbs (36.4 kg).

b. In the presence of known/suspected obstructive disease of the GI tract, including but not limited to diverticulitis and inflammatory bowel disease.

c. In volunteers exhibiting or having a history of disorders or impairment of the gag reflex.

d. In any volunteer with previous GI surgery.

e. In any volunteer having felinization of the esophagus.

f. In volunteers who might undergo NMR or MRI scanning during the period that the CorTemp Core Body Temperature Sensor is within the body.

g. In volunteers with hypomotility disorders or the GI tract, including but not limited to ileus.

h. In volunteers with a cardiac pacemaker or other implanted electromedical device.

Prior to administering the CorTemp pill, the contra-indications will be reviewed to make sure the volunteer is an appropriate candidate.

10. **Overfeeding** – The overfeeding in this study is short-term (2 periods of 3 days each) and is not out of the realm of “normal overeating”. Evidence for this is the food intake data while on the vending machines during the original study (5), where individuals averaged >165% of their weight maintenance energy requirements without adverse effect.

11. **Needle** **biopsy of abdominal wall and femoral adipose tissue and muscle tissue** – The potential hazards of this procedure are a local hematoma or infection at the site of the biopsy. These hazards are greatly minimized by attention to hemostasis, application of local pressure, and proper use of sterile technique. The biopsies are performed in the tangential plane to the abdominal wall so the risk of abdominal cavity puncture or epigastric artery laceration are essentially nil.

12. **Wearable sensors to estimate food intake and mass –** Except for the inconvenience of wearing the strain sensor and swallowing collar, there is no risk associated with these sensors. The IRB at Clarkson University has previously approved the use of the swallowing monitor that will be used in this study. A stationary version of the chewing sensor has also been approved by the Clarkson IRB. We propose to use a slightly modified version of the sensor that allows for free ambulation by volunteers.

13**. Measurement of dietary fat oxidation while in the respiratory chamber -** Deuterium is a stable (non-radioactive) isotope tracer that is given in minute quantities. There is minimal risk associated with this test (70). Deuterium oxide has been used extensively for the measurement of total body water spaces in man (71;72). The natural abundance of deuterium in tap water is 150 ppm and a tracer dose of 4-5 grams in an adult increases this to about 250 ppm. There have been no reports of any signs of toxicity or abnormalities in metabolism using this tracer amount.

**BENEFIT FOR THE PARTICIPANTS**

There is no benefit to the participant for taking part in this study. However, some of the data derived from this study may help us to define some behaviors that put people at greater risk of obesity and its complications. Individuals exhibiting unhealthy behaviors will be offered feedback and counseling to correct these behaviors.

**RESEARCH USE OF HUMAN SAMPLES, SPECIMENS OR DATA**

Blood (stored as plasma or serum) urine, and fat samples not immediately used for study purposes will be stored for future measurements. Stored samples and specimens will be used only to measure factors that relate to diabetes, obesity and their complications. Stored samples, specimens or data may be sent to collaborators for specific measurements or analyses. All stored samples, specimens, and data will be coded so that when sent for measurements the identity of the volunteer remains confidential. Identification of coded samples will be kept in a secure password-protected database accessible only to investigators, but samples will be identifiable in case specific tests yield clinical information of importance to a particular volunteer or so samples can be destroyed per volunteer request (see below). Samples will be used only for research and not for commercial purposes. Research volunteers will not be informed of individual results from analyses performed specifically for research purposes, unless there is clear evidence accepted by the medical community that these results will impact the volunteer’s individual medical care or future health. Samples will be stored until used unless the volunteer requests in writing that the samples be destroyed. Reports of samples lost due to technical issues or destroyed secondary to volunteer request will be included in the annual renewal report.

At this time, there is a collaboration set up with [name], of the Obesity Research Center at the University of Cincinnati’s Genome Research Institute, in Cincinnati, OH, for measuring hormones that may be related to obesity and food intake.

We are collaborating with [name]., of the Umeå University Hospital, Umeå, Sweden. [name] will aid in analysis of spontaneous physical activity data as collected by activity monitors in the overfeeding arm of the study. [name] will receive data from the activity monitors and other metabolic parameters collected during this arm of the study.

We also are collaborating with [name], Unit on Growth and Obesity, National Institute of Child Health and Disease, Bethesda, MD. [name] will measure brain derived neurotrophic factor (BDNF), which may have a role in energy homeostasis. He will measure BDNF in serum and plasma to examine its relationship with energy expenditure, insulin action, and adiposity.

We are collaborating with [name], Associate Professor, Department of Electrical and Computer Engineering, Clarkson University, Potsdam, NY. [name] has developed the wearable chew/swallow sensors for energy intake monitoring that some of our volunteers will wear while eating from the vending machine system. [name] is providing the sensors and training as well as assisting with data analysis and interpretation.

We are also collaborating with [name]., University of California, Irvine, Irvine, CA. [name] will measure endocannabinoids, fatty acids, and fatty acid derivatives in plasma samples from research volunteers participating in this protocol. Analyses will test whether these molecules are related to food intake, choice of foods, meal frequency, macronutrient intake and time of food consumption.

**ADVERSE EVENT REPORTING**

Adverse events that occur as the direct result of the testing procedures in this study will be forwarded to the NIDDK IRB. Since this is not a treatment study, these events are expected to be infrequent. Previously undiagnosed medical conditions discovered by laboratory testing or imaging will not be reported as adverse events, but will receive appropriate follow-up and referral to the primary care provider.

**DATA AND SAFETY MONITORING**

Because this is not an intervention trial, data and safety monitoring issues will be limited to events associated with obtaining the measures for this study. The Principal Investigator will, therefore, serve in this capacity and report these events directly to the NIDDK IRB.

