**Experimental Design:**

In this protocol, we will investigate eating behavior, caloric intake and food preferences. We will utilize questionnaires and methods of assessing eating behavior, measurements in blood, urine, and fat as well as measurements of substrate oxidation to elucidate physiologic mechanisms that underlie caloric intake as well as investigate genetic polymorphisms that may be related to calorie intake or to behaviors or factors that are associated with caloric intake. Volunteers will also be invited to wear a swallowing collar and band-aid chewing sensors, to validate these in the measurement of food intake. In the two study arms, we will investigate eating behavior and food preferences in response to overfeeding or to changes in the macronutrient content of the diet. Most specifically, we will utilize several questionnaires and methods of assessing eating behavior and the preference for high fat foods to create a ‘food intake phenotype’. We will also draw fasting total and active ghrelin concentrations prior to and following a 3-day period of overfeeding by 50% of weight maintenance caloric needs. This will allow us to confirm that overfeeding suppresses fasting ghrelin concentrations. This will be followed by 3 days of *ad libitum* food intake using the computerized vending machine system. In the macronutrient content of the diet study arm, we will assess the effects of a 3-day period of both (in random order) an isocaloric high fat (50% fat, 30% carbohydrate, 20% protein) and an isocaloric high carbohydrate (60% carbohydrate, 20% fat, and 20% protein) diet on subsequent food intake.

To achieve these goals, we will measure the following:

1. Height and weight

2. Body composition by dual energy X-ray absorptiometry (DXA)

3. Oral glucose tolerance

4. Eating behavior using the Gormally binge eating questionnaire and the Stunkard 3-factor eating questionnaire

5. Food preferences using the Drewnowski taste test, the response to PROP tasting (original study only), and the food preferences questionnaire

6. Fat Intake using the Block 2005 food questionnaire to assess usual nutrient intakes and the vending machines (combined with the pretest foods listing) to assess actual intakes

7. Body image perception using the Stunkard body image questionnaire

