**Experimental protocol for ghrelin suppression and food intake substudy:**

**Day 1** -Admission, medical history and physical examination

-Urine collections for complete urinalysis, urinary HCG (for pregnancy status in females), and drug testing (for marijuana, cocaine and amphetamine metabolites)

-Anthropometric assessments including height, weight, waist and thigh circumferences

-12-lead electrocardiogram (ECG)

-Blood drawing for complete blood count, platelet count, prothrombin time, partial thromboplastin time, electrolytes, plasma urea nitrogen, creatinine, calcium, total protein, albumin, SGOT, gamma-GT, alkaline phosphatase, bilirubin, thyroid stimulating hormone (TSH)

-Begin weight maintenance diet with calories distributed as 50% from carbohydrate, 30% from fat, and 20% from protein

-Food preferences questionnaire

**Day 2** -Body composition by dual-energy X-ray absorptiometry (DXA)

-Block 2005 food questionnaire

**Day 3** -Psychological questionnaires and computerized performance tests

**Day 4** -Oral glucose tolerance test

**Days 5-6** -Begin either overfeeding diet at 150% of weight maintenance energy intake with calories distributed as 50% from carbohydrate, 30% from fat, and 20% from protein or weight maintenance diet (floor diet)

-Fasting blood draw for total and active ghrelin and hormones, including thyroid hormones (TSH, FT3, FT4, rT3) and catecholamines (norepinephrine and epinephrine) before starting diet

-Begin wearing Actiheart and Actical (wear for 3 day diet)

**Day 7** -Respiratory chamber while on study diet (either overfeeding at 150% of chamber weight maintenance diet or standard chamber diet) for assessment of 24-hour sedentary energy expenditure and respiratory quotient

-Swallow CorTemp™ sensor and begin wearing temperature monitor (prior to chamber)

-Remove Actiheart and Actical when exiting chamber

**Days 8-10** -Vending machine study

-Fasting blood draw for total and active ghrelin and hormones, including thyroid hormones (TSH, FT3, FT4, rT3) and catecholamines (norepinephrine and epinephrine) before starting diet

-Daily blood draws for total ghrelin and orexigenic/anorexigenic hormones

**Day 11-13** -Begin weight maintenance diet with calories distributed as 50% from carbohydrate, 30% from fat, and 20% from protein for “wash-out” period

- 24-hour food recall (day 11)

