**Experimental protocol for the effect of macronutrient content on food intake:**

Day 1 -Admission, medical history and physical examination

-Urine collections for complete urinalysis, urinary HCG (for pregnancy status in females), and drug testing (for marijuana, cocaine and amphetamine metabolites)

-Anthropometric assessments including height, weight, waist and thigh circumferences

-12-lead electrocardiogram (ECG)

-Blood drawing for complete blood count, platelet count, prothrombin time, partial thromboplastin time, electrolytes, plasma urea nitrogen, creatinine, calcium, total protein, albumin, SGOT, gamma-GT, alkaline phosphatase, bilirubin, thyroid stimulating hormone (TSH), lymphocyte transformation to verify previous genotyping and replenish DNA stores

-Begin weight maintenance diet with calories distributed as 50% from carbohydrate, 30% from fat, and 20% from protein

-Food preferences questionnaire

Day 2 --Body composition by dual-energy X-ray absorptiometry (DXA)

-Block 2005 food questionnaire

Day 3 - Psychological questionnaires and computerized performance tests

Day 4 -Oral glucose tolerance test

Day 5 -Respiratory chamber for assessment of 24-hour sedentary energy expenditure

and respiratory quotient

-Blood draw for total and active ghrelin

Days 6-7-Begin isocaloric diets with changes in macronutrient composition. Subjects

will be randomized to receive either the high carbohydrate (HC: 60%

carbohydrate, 20% protein, 20% fat) or high fat (HF: 50% fat, 30% carbohydrate,

20% protein) diet at their weight maintenance energy intake

Day 8 -Respiratory chamber while receiving their chamber weight maintenance energy

intake (same diet as when on floor – HC or HF) for assessment of 24-hour

sedentary energy expenditure and respiratory quotient

Days 9-11-Vending machine study with daily blood drawing for assessment of

orexigenic/anorexic hormone levels

Day 12-14-Begin weight maintenance diet with calories distributed as 50% from

carbohydrate, 30% from fat, and 20% from protein

-Blood drawing for assessment of orexigenic/anorexic hormone levels

- 24-hour food recall (day 12)

Day 15-16 -Begin isocaloric diet with changes in macronutrient composition. Subjects

will receive the HC or HF diet at their weight maintenance energy intake. Diet

type will depend on which diet was given during days 6-8

Day 17-Respiratory chamber while receiving their chamber weight maintenance energy

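### The safety sections deny that this is an intervention trial and tie monitoring and reporting to tests and measurements, although two arms assign diets in order to study their effects

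*Protocol*

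**What the plan says.** Two short sections set the safety rules, and neither makes an exception for any arm.

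- Data and Safety Monitoring, opening sentence: "Because this is not an intervention trial, data and safety monitoring issues will be limited to events associated with obtaining the measures". The following sentence draws a consequence from this, namely that the principal investigator acts as monitor and reports to the IRB.
- Adverse Event Reporting, opening sentence: "Adverse events that occur as the direct result of the testing procedures in this study will be forwarded to the NIDDK IRB". It adds: "Since this is not a treatment study, these events are expected to be infrequent".

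The design sections describe assigned exposures.

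- Experimental Design says that the two additional arms examine eating behaviour and food preferences "in response to overfeeding or to changes in the macronutrient content of the diet".
- The ghrelin suppression substudy schedule has volunteers begin either an "overfeeding diet at 150% of weight maintenance energy intake" or a maintenance diet, and gives them the other one in the second period.
- The macronutrient schedule says that subjects "will be randomized to receive either the high carbohydrate (HC: 60" (the quotation stops at the percentage) or a high-fat diet, with the second diet depending on the first. Experimental Design confirms that the order is random.
- Possible Risks and Hazards gives overfeeding its own entry, item 10.

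**The concern.** The statement that there is no intervention is more than a label. The monitoring section uses it as the reason for restricting its scope. If the premise fails for two arms, the restriction has no stated basis there.

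An imposed three-day diet is the exposure under study. In ordinary language it is neither a test nor a way of obtaining a measurement. Someone applying the two sections as worded could conclude that an event brought on by the diet itself is outside both rules. No other section gives a rule for such events. What is at stake is whether the IRB and the monitor would learn of harms from the one thing the two diet arms add to the original study.

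**Working it through.** No figure in the plan needs reproducing, so the check is a comparison of text.

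**1. Does the premise fit each part of the study?**

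| Part | Diet imposed to study its effect? | Fits the non-intervention premise? |
|---|---|---|
| Original study | No: maintenance diet, then free choice from vending machines | Yes |
| Overfeeding arm | Yes: 150% of maintenance against a maintenance period | No |
| Macronutrient arm | Yes: high-fat and high-carbohydrate diets in random order | No |

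The Introduction supports the last two rows. It gives the effect of overfeeding as an aim, and it states a directional hypothesis that the high-carbohydrate period will lead to lower subsequent intake than the high-fat period. Random order is stated only for the macronutrient arm. For the overfeeding arm the schedule says only that the second diet depends on the first.

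**2. Do the two rules reach events caused by the diets?**

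| Exposure | Numbered item in Tests and Analyses? | Item in Possible Risks and Hazards? | Forwarding rule (testing procedures) | Monitoring rule (obtaining the measures) |
|---|---|---|---|---|
| Overfeeding | No. Items 13 and 14 are measurements made during overfeeding | Yes, item 10 | Not reached on a literal reading | Not reached |
| High-fat and high-carbohydrate diets | Yes, item 15 | No, none of the 13 items | Ambiguous | Not reached on a literal reading |

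The term testing procedures is not defined. Item 15 therefore leaves room to count the macronutrient diets as tests. Overfeeding has no such entry of its own. The monitoring wording is narrower still, since assigning a diet does not obtain a measure.

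**3. How much of the study is affected?**

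From Sample Size Calculations and Data Analysis: 30 volunteers in the overfeeding arm and 50 in the macronutrient arm, so 30 + 50 = 80.

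From the schedules:
- Overfeeding arm: one three-day overfeeding period, on Days 5-7 or 14-16 of a 20-day stay.
- Macronutrient arm: two three-day diets, on Days 6-8 and 15-17, so 3 + 3 = 6 days of a 21-day stay.

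**4. A related inconsistency.** Item 10 of the risk section says: "The overfeeding in this study is short-term (2 periods of 3 days each" (the quotation stops before the closing bracket). The substudy schedule has one overfeeding period and one maintenance period. The two descriptions of the exposure must be reconciled. The main point does not depend on which is meant.

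**The case against.** The strongest reply is that the rules can be read broadly. Testing procedures is undefined, dietary manipulation is a numbered entry under Tests and Analyses beside the glucose tolerance test and the respiratory chamber, and overfeeding sits in the same hazard list as the tests. This stands in part. A reader might infer that every diet-related event is definitely excluded, and the documents do not support that for the macronutrient diets under the forwarding rule. The reply does not settle overfeeding, which has no entry of its own among the tests, and it does not reach the monitoring sentence, which speaks of obtaining measures.

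Other inferences go further than the text allows:

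- **Diet-related events would go unrecorded.** One section says what is forwarded and the other what is monitored. Neither forbids recording. Volunteers are inpatients, and the eligibility text provides for withdrawal because of illness.
- **The reassurance about overfeeding in the risk section is undermined.** That statement concerns past free intake from the vending machines in the original study. A reporting rule for the new arms cannot remove that evidence.
- **Calling this something other than a treatment study is also wrong.** That phrase is defensible: the volunteers are healthy, no therapy is given, and the protocol states no benefit to them.
- **The principal investigator should not be the monitor.** That role is derived from the disputed premise, but nothing in the documents shows that it is unsuitable.

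It is also fair to say that the exposures are short. The macronutrient diets are isocaloric, and the protocol reports that volunteers eating freely averaged more than 165% of maintenance needs.

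**Conclusion.** The contradiction is real and should be corrected. The non-intervention statement is wrong for two arms, and it is the stated reason for a monitoring scope that, as worded, does not reach the assigned diets. The forwarding rule leaves out overfeeding on a literal reading and is ambiguous for the macronutrient diets.

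The size is 80 planned volunteers, with three or six scheduled days each on an experimental diet. No estimate, randomisation step or hypothesis test is affected, and the protocol plans no tolerability analysis for these arms. The conclusion rests on two assumptions: that testing procedures keeps its ordinary meaning where the protocol does not define it, and that no rule outside this document covers diet-related events.

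**What to change.** - In Data and Safety Monitoring, remove the statement that this is not an intervention trial, or confine it to the original study.
- In both safety sections, state that adverse events related to the assigned diets are monitored and forwarded to the IRB in addition to test-related events. This also settles whether the macronutrient diets count as testing procedures.
- Add to the present rule and do not replace it with a window that opens at the first assigned diet. Such a window would lose events from earlier tests, such as the Day 4 glucose tolerance test in both diet arms and the Day 5 chamber stay in the macronutrient arm. One that also closed at discharge would lose the 6- and 12-month visits.
- The sentence that this is not a treatment study may stay.
- Reconcile the number of overfeeding periods in the risk section with the substudy schedule.

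The cost is a short amendment and slightly more event recording and reporting by unit staff. No diet, schedule or clinical rule changes.
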